# SCANPatient: study protocol for a multi-centre, batched, stepped wedge, comparative effectiveness, randomised clinical trial of synoptic reporting of computerised tomography (CT) scans assessing cancers of the pancreas

**DOI:** 10.1186/s13063-024-08196-5

**Published:** 2024-06-17

**Keywords:** Pancreatic ductal adenocarcinoma (PDAC), Resectability, Computerised tomography (CT) scans, Synoptic reporting, Randomised controlled trial

## Abstract

**Background:**

Complete surgical removal of pancreatic ductal adenocarcinoma (PDAC) is central to all curative treatment approaches for this aggressive disease, yet this is only possible in patients technically amenable to resection. Hence, an accurate assessment of whether patients are suitable for surgery is of paramount importance. The SCANPatient trial aims to test whether implementing a structured synoptic radiological report results in increased institutional accuracy in defining surgical resectability of non-metastatic PDAC.

**Methods:**

SCANPatient is a batched, stepped wedge, comparative effectiveness, cluster randomised clinical trial. The trial will be conducted at 33 Australian hospitals all of which hold regular multi-disciplinary team meetings (MDMs) to discuss newly diagnosed patients with PDAC. Each site is required to manage a minimum of 20 patients per year (across all stages). Hospitals will be randomised to begin synoptic reporting within a batched, stepped wedge design. Initially all hospitals will continue to use their current reporting method; within each batch, after each 6-month period, a randomly selected group of hospitals will commence using the synoptic reports, until all hospitals are using synoptic reporting. Each hospital will provide data from patients who (i) are aged 18 or older; (ii) have suspected PDAC and have an abdominal CT scan, and (iii) are presented at a participating MDM. Non-metastatic patients will be documented as one of the following categories: (1) locally advanced and surgically unresectable; (2) borderline resectable; or (3) anatomically clearly resectable (Note: Metastatic disease is treated as a separate category). Data collection will last for 36 months in each batch, and a total of 2400 patients will be included.

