## Methods: participants, interventions, and outcomes

### Study setting {9}

The trial will be based at 33 Australian hospitals. A list of participating hospitals can be found via the following weblink in the ANZCTR: https://www.anzctr.org.au/ACTRN12623000508673.aspx.

Participating sites will provide data from eligible patients over the 36-month data collection period, with the first batch’s data collection period starting from July 2023.

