### Sample size {14}

Currently 8% of all patients diagnosed with PDAC are categorised with BR disease in the Upper Gastrointestinal Cancer Registry (UGICR; unpublished data) which is operating in most major centres in Victoria and approximately half of the major centres in New South Wales. We hypothesise that with the introduction of a new structured radiology report, leading to increased diagnostic accuracy, this will increase to 15%. This is supported by the final results of the pilot synoptic report study (wherein the rate of BR disease was 13% in the pilot study across 95 patients [12]) and international registry data which have shown that the rate of resection of major vascular structures at the time of surgery for PDAC is between 10 and 15% [14], a surrogate for involvement of those major structures and therefore a pseudo-definition of BR disease. As not all patients with BR PDAC will require formal venous or arterial resection, it is likely the actual rate of BR disease is higher in these larger international and national registries. An increase in the diagnosed rate of BR disease to this level will result in more patients appropriately being given neoadjuvant therapy, and a clinically meaningful change in the standard of care if identified.

The trial was originally designed as a standard, stepped wedge design with 8 hospitals randomised to each sequence of a standard 5-sequence/6-period stepped wedge design (a total of 40 hospitals). With 15 patients per hospital in each 6-month period, assuming a two-sided significance level of 0.05, this design has power ≥ 80% to detect an increase from 8 to 15% in the primary outcome. Power is maintained for a wide range of intracluster correlations and alternative within-cluster correlation structures, e.g. for a discrete time decay within-cluster correlation structure [15], with an intracluster correlation of 0.1 and a cluster autocorrelation of 0.55, power is 84%. Under most within-cluster correlation structure assumptions, power will remain > 76% should hospital recruitment be up to 25% lower and patient recruitment up to 30% lower than expected (i.e. with 10 patients each year in each of 30 hospitals). With the batched variant shown in Table 2, for the extreme scenario considered above (an intracluster correlation of 0.1 and cluster autocorrelation of 0.55), power levels remain > 80%. Sample size calculations were performed using the Shiny CRT calculator [16].

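### The stated total of 2400 patients does not match the inputs of the power calculation, and the stated power above 80% is not reached at 33 hospitals with either total at ICC 0.1 and cluster autocorrelation 0.55

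*Protocol article*

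**What the plan says.** The abstract gives both a duration and a total: "Data collection will last for 36 months in each batch, and a total of 2400 patients will be included". Under Study setting the article says "The trial will be based at 33 Australian hospitals". Trial status gives the batch sizes as 12, 10 and 11 sites.

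The Sample size section works from other figures. The original plan was a "standard 5-sequence/6-period stepped wedge design" with 8 hospitals per sequence, "a total of 40 hospitals", and the accrual input is "With 15 patients per hospital in each 6-month period". For an increase from 8% to 15% at two-sided 0.05, it reports 84% power under discrete time decay with an intracluster correlation (ICC) of 0.1 and a cluster autocorrelation (CAC) of 0.55. It then says that the batched variant keeps power above 80% in that same scenario, which it treats as extreme. It states neither the number of hospitals nor the number of patients behind that last figure. The figure of 2400 does not appear in the section.

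**The concern.** The headline sample size and the power statement are printed in the same article, and a reader will take one to belong to the other. They do not share inputs. The total is lower than 33 hospitals at the planning rate would supply, and the only fully specified power figure is for 40 hospitals. If the total is too low for the stated power, the trial is presented as better powered than it is. If the total is simply out of date, completed recruitment will be judged against the wrong number. Either way, it cannot be seen which sample size the power above 80% refers to.

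**Working it through.** **Totals.** Inputs: 33 or 40 hospitals, 6 periods of 6 months and 15 patients per hospital-period (Sample size, Study setting); site minimum of 20 per year (abstract, Eligibility criteria).

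- Original plan: 40 × 6 × 15 = 3600.
- Current hospitals, planning rate: 33 × 6 × 15 = 2970.
- Current hospitals, site minimum: 33 × 20 × 3 = 1980.
- Low-recruitment case in the Sample size section, 30 hospitals: 30 × 10 × 3 = 900 as printed (10 per year), or 30 × 10 × 6 = 1800 if 10 per period was meant.
- Rate implied by the stated total: 2400 / (33 × 6) = 12.1 per hospital-period. The shortfall is (2970 − 2400) / 2970 = 570 / 2970 = 19%.

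None of these totals is 2400.

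**Power formula.** I used generalised least squares on cluster-period means, with a fixed period effect for each period within each batch. For one hospital with m patients per period, the covariance of its six period means is V = σ²[ICC × CAC^|s−t| + (1 − ICC)/m on the diagonal]. With n_k hospitals in sequence k, treatment vector x_k and N hospitals in the batch, the information on the treatment effect is summed over batches:

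I = Σ_batches { Σ_k n_k x_k′V⁻¹x_k − (Σ_k n_k x_k)′V⁻¹(Σ_k n_k x_k)/N }

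Then SE = 1/√I and power = Φ(0.07/SE − 1.960).

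Two variance conventions were used. One takes the mean proportion: σ² = 0.115 × 0.885 = 0.1018. The other takes the mean of the two variances: (0.08 × 0.92 + 0.15 × 0.85)/2 = 0.1006.

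**The protocol's figure first.** 40 unbatched hospitals, m = 15, ICC 0.1, CAC 0.55: SE = 0.02387, so 0.07/0.02387 − 1.960 = 0.973 and power is 83.5%. The second variance gives SE = 0.02372 and 83.9%. The stated 84% is reproduced.

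**Batched, same ICC and CAC.** Table 2 is not visible, so the split over sequences is assumed: 3/2/2/2/3 for the 12 sites, 2/2/2/2/2 for the 10, and 2/2/3/2/2 for the 11.

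| Design | m | Total | SE (first variance) | Power (two variances) |
|---|---|---|---|---|
| 40 batched | 15 | 3600 | 0.02393 | 83.3–83.7% |
| 33 batched | 15 | 2970 | 0.02624 | 76.1–76.6% |
| 33 batched | 12.1 | 2400 | 0.02751 | 72.1–72.6% |

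The 40-hospital row assumes splits of 3/3/2/3/3, 2/3/3/3/2 and 3/2/3/2/3. If the extra sites in the batch of 12 go to sequences 2 and 4 instead, the two 33-hospital rows fall to about 75–76% and 71–72%.

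**Other correlations, 33 batched hospitals, first variance, discrete time decay.**

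| ICC / CAC | 2970 patients | 2400 patients |
|---|---|---|
| 0.05 / 0.55 | 88.1% | 84.0% |
| 0.05 / 0.8 | 90.6% | 86.0% |
| 0.1 / 0.8 | 83.9% | 78.9% |

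**Where the loss comes from at 0.1 / 0.55.** Going from 40 unbatched to 33 batched hospitals at m = 15 costs 83.5 − 76.1 = 7.4 points, nearly all of it from the smaller number of hospitals. Going from 2970 to 2400 patients costs a further 76.1 − 72.1 = 4.0 points.

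**The case against.** Several counter-arguments carry weight.

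- **The power conflict is confined to high ICC.** The protocol itself treats ICC 0.1 with CAC 0.55 as extreme, and at ICC 0.05 either total exceeds 80%. This stands and limits the finding. The claim of more than 80% is, however, made for exactly that extreme scenario.
- **Most of the shortfall is not due to 2400.** This also stands. About 7 of the 11 points come from the number of hospitals, so replacing 2400 by 2970 would not by itself restore 80%.
- **Lower recruitment was anticipated.** The Sample size section considers hospitals up to 25% and patients up to 30% below plan. Here hospitals are 17.5% and patients per period 19% below. That passage claims more than 76% under most structures, which is a weaker statement than the one made for the batched design.
- **Other modelling choices are kinder.** With a block-exchangeable structure at 0.1 / 0.55, 33 hospitals reach 82% with 2970 patients and 78% with 2400. But the scenario the protocol refers back to is discrete time decay. Using the control-arm variance alone gives 88% and 85%, but it also gives 93% for the 40-hospital plan and so does not match the protocol's 84%.
- **The full protocol may derive 2400.** It may. The article still prints a total and power inputs that disagree.

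A reader might infer three stronger things, which the document does not support.

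- *Recruitment would stop at 2400, before the last hospitals switch.* No cap is stated. The article fixes 36 months per batch and includes all eligible patients. Even with a cap and 15 per period, the staggered starts give 2.5 × [12t + 10(t − 2) + 11(t − 4)] = 2400, so t = 31.0 months from July 2023, after the first batch's last switch at month 30. Below about 13.6 per period, 2400 is not reached before the third batch's last switch at month 34.
- *The plan has two conflicting end rules.* A fixed duration with an expected total is one rule and one forecast.
- *2400 is a leftover from 40 × 20 × 3.* The product matches, but no text says so. 2400 is also 24.2 per hospital per year, between the minimum of 20 and the planning rate of 30, so it could equally be an accrual forecast.

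**Conclusion.** The concern holds in a limited form. The stated 2400 is 570 patients (19%) below the 2970 implied by 33 hospitals at the planning rate, and the article does not explain it. In the protocol's own ICC 0.1 / CAC 0.55 scenario, 33 batched hospitals give about 76% power with 2970 patients and about 72–73% with 2400, not more than 80%. At ICC 0.05 power stays above 80% with either total. At ICC 0.1 / CAC 0.8 the choice of total decides on which side of 80% it falls.

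The totals are plain arithmetic. The power figures rest on near-equal splits over sequences, equal hospital sizes, discrete time decay and a normal approximation. The same method reproduces the stated 84%. Power above 80% is reproduced for 40 batched hospitals, which suggests, but does not prove, that the batched claim was computed for 40. The design, randomisation and duration of the trial are not called into question.

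**What to change.** In the abstract and the Sample size section:

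1. Give one expected total with its derivation: either 2970 (33 × 6 × 15), or 2400 with the rate of about 12.1 per hospital-period stated as the planning input.
2. Restate the power for 33 batched hospitals at that total and name the hospital count, rate and correlation structure. At ICC 0.1 / CAC 0.55 this is about 76% for 2970 or about 72–73% for 2400, to be recomputed with the actual allocation in Table 2. The figures at milder correlations can be given beside it.
3. Confirm that the 36 months of data collection per batch governs, and that the total is an expectation and not a cap.

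The cost is a wording change in the protocol, carried over to the registry entry where it gives the same figures, and a less favourable power figure in the extreme scenario. Nothing changes in randomisation, data collection or analysis.

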**Discussion:**

Better classifying patients with non-metastatic PDAC as having tumours that are either clearly resectable, borderline or locally advanced and unresectable may improve patient outcomes by optimising care and treatment planning. The borderline resectable group are a small but important cohort in whom surgery with curative intent may be considered; however, inconsistencies with definitions and an understanding of resectability status means these patients are often incorrectly classified and hence overlooked for curative options.

**Trial registration:**

The SCANPatient trial was registered on 17th May 2023 in the Australian New Zealand Clinical Trials Registry (ANZCTR) (ACTRN12623000508673).

**Supplementary Information:**

The online version contains supplementary material available at 10.1186/s13063-024-08196-5.

## Administrative information

Note: the numbers in curly brackets in this protocol refer to SPIRIT checklist item numbers. The order of the items has been modified to group similar items (see http://www.equator-network.org/reporting-guidelines/spirit-2013-statement-defining-standard-protocol-items-for-clinical-trials/).

## Introduction

### Background and rationale {6a}

Approximately 4000 Australians are diagnosed with pancreatic cancers annually, over 80% of which are pancreatic ductal adenocarcinoma (PDAC) [1, 2]. Despite recent advances in treatment, overall survival in people with PDAC remains poor, with a 5-year survival across all stages of only 11% [2]. With no screening test for early detection of PDAC currently available [3], there is an urgent need to improve these outcomes particularly as it is predicted that PDAC will become the second most common cause of cancer death by the end of this decade [1–3]. Between half and two-thirds of patients present with metastatic disease at diagnosis [1–3]. Of those without obvious metastases at diagnosis, tumours are assessed as to their resectability according to the degree of major vascular involvement by the tumour [3]. Conventionally, major arterial resection has not been performed during pancreatic resections due to concerns about operative and oncologic risks. As such, non-metastatic disease may be categorised as (1) locally advanced (LA) and therefore initially unresectable without major vascular reconstruction; (2) borderline resectable (BR) due to some degree of vascular involvement; or (3) clearly resectable (CR) based on no major vascular involvement [3].

Stratification into LA, BR and CR which determines optimal treatment (Fig. 1) requires high-quality, cross-sectional radiological imaging using computed tomography (CT) using a dedicated “CT pancreas protocol” [3]. Magnetic resonance imaging (MRI) scans may also be used to help discriminate the extent of localised disease but CT is the current “gold” standard. The respective percentages of tumours in each of these categories (CR, BR or LA) in any given cohort around the world are uncertain [4], given differing published definitions of each subtype, as well as known variation in the interpretation of CT scans by radiologists and pancreatic surgeons [5]. For example, in radiologic staging, the following factors may contribute to variability: scanner (e.g. image quality, specific protocols or contrast timing); accuracy of findings (radiologist awareness and experience); documentation of findings (clarity and completeness); context (timing of scans vs cytologic diagnosis); and synthesis (determining status from finding) [6].

**Fig. 1 Fig1:**
[figure not shown]
Stratification and treatment options for people diagnosed with pancreatic cancer

These issues have confounded interpretation of findings both within and across cohorts [7–11], which has led to inability to directly compare international treatment trials or ensure consistent recommendations between MDT meetings in different sites or jurisdictions. However, the use of a standard synoptic report may assist in reproducible consistency and validity [7–11], objectives this study aims to assess.

In an attempt to minimise variation in assessment of resectability of PDAC, our group conducted a small-scale pilot study in which we developed and tested a synoptic report for PDAC derived from the International Consensus Guidelines on Surgical Resectability [11] at two metropolitan pancreatic cancer services in Melbourne, Victoria [12]. The study found that the use of a synoptic report was feasible and had the potential to improve the classification of resectability [12]. Building on the experience and findings of the pilot study, we plan to trial the synoptic radiological report Australia-wide. We plan to use a comparative effectiveness (CE) randomised clinical trial (RCT) design to assess its utility against current standards of care to test whether this approach increases the proportion of PDAC categorised as BR, through structured assessment of vascular involvement.

### Objectives {7}

The primary objective of this trial is to determine the difference in the proportion of patients diagnosed with BR PDAC before and after introduction of the synoptic radiology report template. There are a number of secondary objectives. The description of objectives, together with the specific outcomes and timepoints are summarised in Table 1.

**Table 1 Tab1:** Objectives, specific outcomes of the SCANPatient trial

Outcome	Rationale (description of primary and secondary objectives)	Source of data	Timepoint(s)
***Primary***			
Patients diagnosed with BR PDAC	To determine the change in the proportion of patients diagnosed with BR PDAC before and after introduction of the synoptic report	SCANPatient REDCap Database	At the time of each patient’s assessment
***Secondary***			
Patients diagnosed with CR PDAC	To determine the change in the proportion of patients with CR in a prospective cohort of patients with PDAC	SCANPatient REDCap Database	At the time of each patient’s assessment
Patients diagnosed with BR PDAC	To determine the change in the proportion of patients with BR in a prospective cohort of patients with PDAC	SCANPatient REDCap Database	At the time of each patient’s assessment
Patients diagnosed with LA PDAC	To determine the change in the proportion of patients with LA in a prospective cohort of patients with PDAC	SCANPatient REDCap Database	At the time of each patient’s assessment
Patients with CR PDAC planned to receive neoadjuvant chemotherapy	To determine the change in the proportion of patients with CR PDAC planned to have neoadjuvant chemotherapy	MDT summary	At the time of the MDT
Patients with BR PDAC planned to receive neoadjuvant chemotherapy	To determine the change in the proportion of patients with BR PDAC planned to have neoadjuvant chemotherapy	MDT summary	At the time of the MDT
Patients with LA PDAC planned to receive neoadjuvant chemotherapy	To determine the change in the proportion of patients with LA PDAC planned to have neoadjuvant chemotherapy	MDT summary	At the time of the MDT
Patients undergoing R1 resection	To determine the change in the proportion of patients undergoing R1 resection (microscopic margin positivity)	SCANPatient REDCap Database	At the time of surgery (if undertaken)
Patients undergoing R2 resection	To determine the change in the proportion of patients undergoing R2 resection (macroscopic margin positivity)	SCANPatient REDCap Database	At the time of surgery (if undertaken)
Patients surgery is abandoned	To determine the change in the proportion of patients whose surgery is abandoned intraoperatively	Surgical operation report	At the time of surgery (if undertaken)
Patient’s management strategy changed	To determine the change in the management strategies for patients with CR, BR and LA PDAC	MDT summary	At time of MDT
Patients with CR PDAC survival status	To determine the overall survival rate for patients with CR localised PDAC	Sites and the national death registry	6 months post completion of recruitment at end of trial
Patients with BR PDAC survival status	To determine the overall survival rate for patients with BR localised PDAC	Sites and the national death registry	6 months post completion of recruitment at end of trial
Patients with LA PDAC survival status,	To determine the overall survival rate for patients with LA localised PDAC	Sites and the national death registry	6 months post completion of recruitment at end of trial
Satisfaction of specialists with synoptic report	To determine the satisfaction of radiologists and HPB (hepatobiliary) surgeons involved in this trial	Health service survey	Prior to the introduction of synoptic reporting and 6 months post commencing synoptic reporting
Synoptic report used routinely as standard of care	To determine the extent to which the synoptic reports for PDAC has become standard of care in routine MDT meetings and whether this model has been incorporated into in-house RIS/PACS (radiology information systems and picture archiving and communication systems)	Health service survey	6 months after trial complete

We hypothesise that the introduction of the synoptic radiological template report will alter (increase) the rate of diagnosis of BR PDAC from baseline.

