## Statistical methods

### Statistical methods for primary and secondary outcomes {20a}

Results will be reported according to the CONSORT extension for stepped wedge trials [17]. Baseline data will be presented in a tabular form with mean and standard deviation or median with lowest and highest values, or percentages and counts as appropriate, by treatment group. We will also present baseline data by hospital and time period.

Results will be compared between *standard reporting* and *synoptic reporting* phases. All available primary and secondary outcomes will be analysed at the patient level using mixed-effects regression models with random intercepts for each cluster in each period, assuming a discrete time decay within-cluster correlation structure (where possible), a fixed effects for the intervention and separate fixed effects for period within each batch [15], or binary outcomes, log-binomial models will initially be fitted; should these fail to converge, mixed-effects Poisson regression models will be fitted, with robust variance estimation. Results will be presented as relative risks with 95% confidence intervals, and as risk differences with 95% confidence intervals. The sensitivity of results to the assumed within-cluster correlation structure will be assessed by fitting models with random effects for each cluster only, and for each cluster-period within cluster. Estimated intracluster correlations and cluster autocorrelations will be reported. The survival outcome will be analysed using a Cox proportional hazards model including shared frailty terms for cluster. All tests will be two-sided. Analyses will be conducted in Stata v 17 or later or in R version 4.2.1 or later as appropriate.

A statistical analysis plan will be prepared and finalised prior to the dataset being released to the statistician.

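### Neoadjuvant planning and overall survival are defined only within CR, BR and LA, categories that the synoptic report assigns and is expected to shift, so between-phase contrasts within them are not protected by randomisation

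*Protocol article*

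**What the plan says.** Table 1 (Objectives) has three neoadjuvant rows, one per resectability category. The first reads "To determine the change in the proportion of patients with CR PDAC planned to have neoadjuvant chemotherapy"; the BR and LA rows follow the same form. Three survival rows have the same split, the first being "To determine the overall survival rate for patients with CR localised PDAC". The row on management strategy also refers to the three categories. No row gives neoadjuvant planning or survival over the whole cohort.

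Under Intervention description, the radiologist determines resectability status by completing the synoptic report. Background and rationale states the purpose as "to test whether this approach increases the proportion of PDAC categorised as BR". Sample size puts figures on this: "Currently 8% of all patients diagnosed with PDAC are categorised with BR disease", and with the structured report, "leading to increased diagnostic accuracy, this will increase to 15"%. The same section expects the rise to lead to more patients being given neoadjuvant therapy.

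Statistical methods compares the standard and synoptic reporting phases: "All available primary and secondary outcomes will be analysed at the patient level using mixed-effects regression models". Survival is to be analysed with a Cox model with shared frailty for hospital. The section does not say whether that model is fitted within category or over all patients. The article describes no common reading of scans that would define the categories alike in both phases, and gives no caveat on stage migration.

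**The concern.** Randomising the time at which hospitals switch makes the patients of the two phases comparable as whole groups, after allowance for period. It does not make the CR patients of one phase comparable with the CR patients of the other when the label is assigned after the switch and by the intervention. A denominator of this kind is itself an outcome of the intervention.

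Two errors can follow. Category-specific rates can change although every patient has the same plan and the same survival as before (stage migration). Conversely, the gain that the plan expects, more patients given neoadjuvant therapy, is a statement about the whole cohort, and no listed outcome measures it. The categories are fixed in Table 1, so an analysis plan that follows Table 1 faithfully inherits the problem.

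**Working it through.** **1. The plan's own figure.** Sample size states 84% power for the original 40-hospital design (8 to 15%, 15 patients per hospital-period, intracluster correlation 0.1, cluster autocorrelation 0.55, "assuming a two-sided significance level of 0.05"). I used a generalised least squares calculation with fixed period effects. The covariance of hospital-period means was 0.1·v·0.55^|s−t|, plus 0.9·v/15 on the diagonal, with v the mean of p(1−p) at 8% and 15%. Power = Φ(0.07/SE − 1.96) = 83.9%, or 83.5% with the pooled proportion. The figure reproduces. The present point concerns how secondary outcomes are defined, not this calculation.

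**2. How much of the BR group is new.** If BR rises from 8 to 15 per 100 patients and all movement is into BR, then (15 − 8)/15 = 7/15 = 47% of synoptic-phase BR patients would have had another label under standard reporting. A smaller rise gives a smaller share.

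**3. Formulas.** Per 100 PDAC patients, let n be a category's standard-phase size. Let f_C and f_L be the numbers moved to BR from CR and LA, with f_C + f_L = 7. Let r be the rate in those who keep their label and m the rate in those who move. Each patient's own plan and outcome are held fixed.

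- CR: standard [(n_C − f_C)·r_C + f_C·m_C]/n_C; synoptic r_C. LA likewise.
- BR: standard r_B; synoptic (8·r_B + f_C·m_C + f_L·m_L)/15.
- Whole cohort: the same patients in both phases, so no change.

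**4. Central illustration.** The article gives none of the following, so they are assumptions: CR 20, LA 15 (BR 8 is the plan's figure); 3.5 moved from each of CR and LA. Rates are in the order stay-CR, CR-to-BR, original BR, LA-to-BR, stay-LA. Neoadjuvant plan: 15, 40, 70, 60, 50%. Survival at 12 months: 80, 65, 60, 50, 40%.

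| | Neoadjuvant, standard → synoptic | 12-month survival, standard → synoptic |
|---|---|---|
| CR | (16.5×0.15 + 3.5×0.40)/20 = 19.4% → 15.0% | (16.5×0.80 + 3.5×0.65)/20 = 77.4% → 80.0% |
| BR | 70.0% → (5.6 + 1.4 + 2.1)/15 = 60.7% | 60.0% → (4.8 + 2.275 + 1.75)/15 = 58.8% |
| LA | (11.5×0.50 + 3.5×0.60)/15 = 52.3% → 50.0% | (11.5×0.40 + 3.5×0.50)/15 = 42.3% → 40.0% |
| All 43 | 17.325/43 = 40.3% in both | 26.625/43 = 61.9% in both |

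**5. Range.** Same rates, with CR 12 to 22 and LA 13 to 20. With BR 8 this makes 33 to 50% non-metastatic, in line with the half to two-thirds metastatic given in Background and rationale. The source of the 7 runs from all CR to all LA. Hazard ratios (HR) are approximated as ln(synoptic survival)/ln(standard survival).

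- BR neoadjuvant: 70% → 65.3% (all from LA) to 56.0% (all from CR), a fall of about 5 to 14 points.
- CR neoadjuvant: no change (all from LA) to (5×0.15 + 7×0.40)/12 = 29.6% → 15.0%, a fall of 0 to 15 points.
- Survival HR: CR 0.66 to 1.00; LA 1.00 to 1.16; BR ln(0.623)/ln(0.60) = 0.93 (all from CR) to ln(0.553)/ln(0.60) = 1.16 (all from LA).

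With different rates the pattern changes. In the central case, if those who move have exactly the rate of the group they leave, only BR shifts, from 70% to 52.5%. If all groups share one rate, nothing shifts.

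**6. A real gain hidden.** Assume 20 CR patients with 20% planned for neoadjuvant therapy and 8 BR patients with 70%. Seven move from CR to BR and their rate truly rises from 20% to 60%. Over the 28 patients, planning rises from (4 + 5.6)/28 = 34.3% to (2.6 + 4.2 + 5.6)/28 = 44.3%. By category, CR stays at 20% and BR falls from 70% to (5.6 + 4.2)/15 = 65.3%. The listed outcomes would show no gain in CR and a loss in BR.

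**The case against.** Several objections have force.

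- **Survival rows.** They speak of determining a rate, not a change, and can be read as description by category. Statistical methods refers to a single survival outcome without mentioning category. This stands: the between-phase contrast is explicit for the three neoadjuvant rows and only inferred for the three survival rows.
- **Certainty and direction.** A reader might infer that bias is certain once BR labelling shifts, or that survival will appear to improve in both CR and BR. The documents support neither. Bias also needs reclassified patients to differ from the group they leave or join. That is likely, since Background and rationale says the category determines treatment, but it is not shown. An apparent gain in both groups arises if migrants come from CR with intermediate survival. The Discussion describes misclassified borderline patients as overlooked for curative options, which suggests that some would come from LA, and BR survival could then fall.
- **Source of the label.** Table 3 takes resectability status from the multidisciplinary meeting (MDM) report as well as the radiology report, and records it again post-operatively. This may soften the problem but does not remove it, because the meeting sees the report.
- **Other surgical outcomes.** A reader might extend the point to R1 resection, R2 resection and abandoned surgery. Those rows carry no category condition, so the point does not reach them.
- **Usefulness.** Category-specific plans still show whether planning matches the label. That is a reason to keep them as description.

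**Conclusion.** The point holds for the three neoadjuvant rows as written, and for the three survival rows if the phase comparison and the Cox model are applied within category. These contrasts condition on a label that the intervention assigns and is meant to change, so randomisation does not protect them.

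Their size cannot be fixed from the article. It gives no CR or LA shares, no source of reclassified patients and no category-specific rates, so the ranges under working rest on assumed values. The direction for BR survival is open. What follows from the plan's own figures is that 47% of the synoptic-phase BR group would be newly labelled, if the full rise from 8% to 15% occurs and all movement is into BR. Over a denominator that the report cannot alter, the artefact is zero by construction.

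The primary outcome, the BR proportion itself, is unaffected.

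**What to change.** In Table 1 and the statistical analysis plan, make neoadjuvant planning and overall survival over all eligible MDM patients the between-phase comparisons. Add the same two outcomes over all non-metastatic patients as a less diluted supporting analysis, noting that metastatic labelling could also shift with the report. Keep the CR, BR and LA results as descriptive, with a sentence that stage migration can change them when no patient's plan or outcome has changed. State which population the Cox model uses. R1, R2 and abandoned surgery need no change on this ground.

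The cost is wording and a protocol amendment. Table 3 already collects treatment plans and survival, recruitment runs to about September 2026, and the analysis plan is to be finalised before data release. Made after results are seen, the same change would be post hoc.

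The drawback is dilution by patients whose category could not change. In step 6 of the working, the gain is 12.4 − 9.6 = 2.8 patients. On the central assumed shares that is 2.8/43 = 6.5 points among non-metastatic patients and 2.8 points among all 100.
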